### Intervention and comparison

All patients will be given interventions based on conventional treatment. During the baseline period, all medications used by the subject to treat COPD and other underlying conditions will be recorded in detail on a case report form (CRF), including the name of the medication, the dose used, the frequency of use, the route of administration, and the start and end times. Any changes in the subject's medication throughout the study will also be recorded in detail. Medications used by patients to treat COPD will be categorized based on GOLD guideline criteria. A respiratory medicine specialist will assess the possibility of continuing acupuncture treatment during acute exacerbations. If a patient is hospitalized for an acute exacerbation, treatment will be continued 1 week after discharge, and the number of treatments delayed due to hospitalization will be replenished. During the study, we will discourage patients from using medications outside the guidelines to treat COPD, including herbal ones. However, if the patient has already used them, they must be documented accordingly.

The classification of basic therapeutic drugs is based on the 2023 GOLD guideline criteria: beta2 agonists (including fenoterol, levosalbutamol, formoterol, salmetero), anticholinergics (including ipratropium bromide, adiponium bromide), and short-acting beta2 agonists and anticholinergics in combination with inhalation devices (including fenoterol/ipratropium bromide, salbutamol/ipratropium bromide), long-acting beta2 agonists and anticholinergic combination inhalation devices (including formoterol/adiponium bromide, formoterol/glumonium bromid), methylxanthines (including aminophylline, theophylline), long-acting beta2 agonists in combination with hormonal inhalation devices (including formoterol/beclomethasone, formoterol/budesonid), and phosphodiesterase-4 inhibitors (including roflumilast).

The treatment protocol was developed based on the preliminary literature collation and a consensus meeting of acupuncture experts. 7 pairs of commonly used and effective acupoints for the treatment of COPD were selected, including bilateral Zhongfu (LU1), Dingchuan (EX-B1), Feishu (BL13), Pishu (BL20), Shenshu (BL23), Zusanli (ST36), and Fenglong (ST40). The acupuncture group and the sham acupuncture group used the same acupoints. Details of each acupoint are shown in Table 2 and Fig. 2. The acupuncturists are licensed and have at least 3 years of clinical experience. All acupuncturists will receive training on acupoint positioning and manipulation before the trial. Each sub-center is assigned an acupuncturist responsible for treating all patients within that center. The acupuncture and sham-acupuncture groups will use a rubber base on the acupoints and perform needling (lifting, thrusting, twisting and rotating manipulation) at 10-min intervals to achieve a better blinding effect.

**Table 2 Tab2:** Locations of acupoints

Acupoints	Locations
Zhongfu (LU1)	On the upper lateral chest, 6 cun from the middle of the chest, level in the first intercostal space
Dingchuan (EX-B1)	0.5 cun lateral to DU14
Feishu (BL13)	1.5 cun lateral to the depression below the spinous process of the 3th thoracic vertebra
Pishu (BL20)	1.5 cun lateral to the depression below the spinous process of the 11th thoracic vertebra
Shenshu (BL23)	1.5 cun lateral to the depression below the spinous process of the 2th lumbar vertebra
Zusanli (ST36)	3 cun directly below ST35, and one finger-breadth lateral to the anterior border of the tibia
Fenglong (ST40)	One finger-breadth lateral to ST38, and at the midpoint of the line joining ST35 and the tip of the external malleolus

**Fig. 2 Fig2:**
[figure not shown]
Locations of acupoints

### Manual acupuncture (MA) group

There are 3 acupuncture groups, which include once a week acupuncture group, twice a week acupuncture group and three times a week acupuncture group. The patient remains prone during acupuncture, and a soft pillow is placed on the front of the patient's chest to elevate the front of the chest to facilitate needling. The acupuncturist will sterilize the skin around the acupoint using 75% alcohol, then attach a rubber base to the acupoint and insert the needle through the rubber base into the acupoint. For LU1, a 1 cun needle (0.25 × 25 mm, Suzhou Hua Tuo, China) is used, and the needle is inserted in a lateral direction for approximately 15–20 mm. The needle is angled at 45° toward the spine for the dorsal acupoints. BL13 is inserted with a 0.5 cun needle (0.25 × 13 mm, Suzhou Hua Tuo, China) for approximately 5–10 mm. EX-B1 and BL20 are inserted with a 1 cun needle (0.25 × 25 mm, Suzhou Hua Tuo, China) for approximately 15–20 mm. BL23, ST36, and ST40, using a 1.5-inch needle (0.25 × 40 mm, Suzhou Huatuo, China), are inserted for approximately 25- 30 mm. After piercing the needle, gentle lifting, thrusting, swirling, and rotating movements are performed on the needle body to achieve *deqi* sensation (soreness, numbness, distension, or heaviness) [30]. The patient's degree of *deqi* sensation will be assessed immediately after the patient has *deqi* sensation [31]. The needles will be retained for 30 min each time, and *deqi* sensation operation will be performed every 10 min, about 15 s each time. When removing the needle, the acupuncturist uses a dry, sterilized cotton ball to gently press the needled area to avoid bleeding.

Once a week acupuncture group: needling once a week with 6-day intervals, 12 times for 12 weeks. Twice a week acupuncture group: 2 needling sessions per week, with a 3-day interval between needling sessions, for 24 needling sessions over 12 weeks. Three times a week acupuncture group: 3 times a week with 1-day intervals for 36 needling sessions over 12 weeks.

### Sham acupuncture (SA) group

The SA group will receive placebo acupuncture in bilateral LU1、EX-B1、BL13、BL20、BL23、ST3, and ST40 on a treatment protocol similar to the acupuncture group. The frequency of the SA treatment is three times a week, with a one-day interval between each treatment, for a total of 36 treatments over 12 weeks. After routine skin disinfection, a rubber soft pad is adhered to the acupoint. A disposable blunt needle (0.3 × 0.13 mm) is used to pierce the base of the rubber soft pad so that the needle body is fixed vertically on the patient's skin. The patient will feel pain but without puncturing the skin. The treatment is simulated by twisting, turning, lifting, and inserting manipulation every 10 min during the treatment, gently swinging the needle body, but without producing a *deqi* sensation. The needles are left for 30 min. Considering the ethical requirements, a free compensatory acupuncture treatment will be given at the end of the trial (Fig. 3).

**Fig. 3 Fig3:**
[figure not shown]
Illustration of acupuncture. a. Needle handle; b. Needle body; c. Plastic cover; d. Blunt tip of the placebo needle; e. Skin; f. Needle tip

### Waiting-list control group

No change in the original primary treatment of COPD patients and no acupuncture intervention will be given. Patients will be required to complete the appropriate tests and scale assessments at the appropriate time points and be given free acupuncture treatment at the end of the trial.

### Blinding assessment

To verify the success of blinding, participants will be asked at the end of the 12-week treatment to answer the question: “do you think you received a traditional acupuncture treatment? (Yes or no).

### Outcome measurements

The outcome measurements and the evaluation times for these measurements are listed in Table 1.

#### Primary outcome

The primary outcome is the proportion of responders at week 12. Responder is defined as participants with a ≥ 4-unit decline in total SGRQ score compared with baseline. A decline of at least 4 points in the total SGRQ score has been determined to be the minimal clinically important difference (MCID) [32]. ≥ 4-unit worsening of SGRQ total score was associated with increased risk of death. The SGRQ is one of the most widely used scales for measuring health impairment and quality of life in adult patients with respiratory diseases, including 1. symptoms (frequency and severity of symptoms); 2. activity (ability to cause breathlessness or limitation of activity due to breathlessness); and 3. impact on daily activities (impairment of social competence and psychological impairment due to airway disease). The above 3 main aspects are scored according to the weights of different questions to obtain the symptom score, activity score and impact score, and finally, the total score is summarized. Higher patient scores indicate poorer quality of life [33]. SGRQ scores will be evaluated at weeks 0, 4, 8, and 12 of enrollment and every 3 months during the follow-up period.

#### Secondary outcomes

Secondary outcomes included the following eight items: 1) the proportion of responders at week 64; 2) change in the SGRQ Scale; 3) change in the mMRC Scale; 4) change in the CAT Scale; 5) change in the Lung Function Screening Indicators (including FEV1, FEV1%pre, FVC and FEV1/FVC); 6) change in the 6MWD;7) change in SF-36 Scale; 8) the number of moderate and severe acute exacerbations during the follow-up period.

The mMRC consists of five grades (0 to 4) and contains statements that describe a range of physical limitations associated with dyspnea. It measures the degree to which a person has dyspnea during activities (such as "strenuous exercise") or limits a person's behavior (such as "too breathless to leave the house") [34]. The CAT consists of 8 items that involve breathing (cough, phlegm, chest tightness, and dyspnea) and other symptoms (low energy levels, sleep disturbances, limitations in daily activities, and confidence when leaving home). Item response values ranging from 0 to 5 (0 = no impairment). The total score was obtained by summing the response values for each item (ranging from 0 to 40). Higher scores indicate a greater impact of the disease on the patient's health and life [35]. Within the CAT, 0–9 is considered a low impact, 10–20 is considered a moderate impact, 21–30 is considered a high impact, and 31–40 is considered a very high impact [36]. Pulmonary function test will be evaluated at weeks 0, 12 and the end of follow-up. Pulmonary Function Test is the gold standard for COPD diagnosis and severity grading. The main indices to be collected include: forced expiratory volume in one second (FEV1), FEV1%pred, forced vital capacity (FVC) and FEV1/FV [37]. The 6-MWD will be evaluated at 12 weeks of enrollment and every 3 months during the follow-up period. The 6MWT is a test commonly used to objectively assess functional exercise capacity in patients with moderate-to-severe pulmonary disease. In the test, patients are asked to walk along a 30-m corridor for as for as possible for 6 minutes [38]. The SF-36 is used to measure self-reported health-related quality of life (HRQOL). SF-36 consists of 36 main questions covering 8 aspects (physical functioning, role physical, bodily pain, general health, vitality, social functioning, role emotional, and mental health). The total score is 0–100, with higher scores representing better quality of life [39]. An acute exacerbation of COPD is defined as an acute worsening of respiratory symptoms (increased dyspnea, cough and sputum purulence) that results in additional therapy [37, 40]. A mild exacerbation refers to patients treated with short-acting bronchodilators (SABDs) plus antibiotics and/or oral glucocorticoids; a severe exacerbation refers to patients requiring hospitalization or emergency care. We will count the number of mild/severe acute exacerbations in the next year for all subjects after the end of treatment. The mMRC, CAT, SF-36 scales, and number of acute exacerbations will be evaluated at weeks 0, 4, 8, and 12 of enrollment and every 3 months during the follow-up period. Data will be collected on 6-MWD at weeks 0 and 12 of enrollment and every 6 months during follow-up. Pulmonary function tests will be performed at weeks 0 and 12 of enrollment and at the end of the 1-year follow-up.

### Safety assessment

Theoretically, the most serious adverse reaction during needling is pneumothorax, so we have developed a strict procedure during the trial, including the selection of different lengths of needles, strict direction and depth of acupuncture. During acupuncture, patients may experience adverse reactions such as needle sickness, subcutaneous hemorrhage, hematoma, severe pain, infection, and needle breakage. Adverse events (AEs) that occur throughout the study will be recorded and reported, and patients will be treated promptly and reasonably. The occurrence, symptoms, duration, severity, treatment measures and disappearance time of AEs will be recorded in detail. When adverse reactions occur, clinicians judge whether to discontinue the trial based on the condition and report severe cases to the Project Management Office of Chengdu University of Traditional Chinese Medicine and the Ethics Committee within 24 h.

### Sample size calculation

As reported in previous studies [15, 41], the mean improvement in SGRQ was -7.1 for patients in the three times a week acupuncture group, the mean change in SGRQ was -2 for patients in the SA group, the mean change in SGRQ was -0.8 for patients in the blank control group, with a standard deviation of 14.2. Using a two-tailed test with a category 1 error of 0.05 and a statistical efficacy of 80%, a sample size of 88 cases per group was calculated, with a maximum of 20% of subjects allowed to drop out or disengage for a required sample size of 110 cases per group. The once a week and twice a week acupuncture groups were set up with the same sample size as the three times a week acupuncture groups, and a total of 550 subjects were included.

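### The sample size is calculated on mean SGRQ change, a secondary outcome, so the stated 80% power does not apply to the primary responder outcome

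*Protocol article*

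**What the plan says.** In the protocol article, Primary outcome: "The primary outcome is the proportion of responders at week 12". The outcome is binary: "Responder is defined as participants with a ≥ 4-unit decline in total SGRQ score compared with baseline". The Statistical analysis section assigns it a generalized linear mixed model. Change in SGRQ is listed under Secondary outcomes.

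The Sample size calculation section uses continuous inputs only. For the most frequent schedule it takes a published figure: "the mean improvement in SGRQ was -7.1 for patients in the three times a week acupuncture group". The corresponding means are -2 for sham and -0.8 for the blank control, and one SD of 14.2 serves all arms. The error rate and target power are then set: "Using a two-tailed test with a category 1 error of 0.05 and a statistical efficacy of 80" per cent. The section reports the result as follows: "a sample size of 88 cases per group was calculated". Allowing 20% dropout, this becomes 110 per group. The two lower-frequency acupuncture arms are given the same size, for 550 in total. The section gives no responder proportion, and it names neither the test nor the comparison to which the 80% belongs.

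**The concern.** The power statement and the primary outcome concern different quantities. Reducing a change score to response or non-response at a 4-unit cut discards information, so a sample that is adequate for the mean is generally too small for the proportion.

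This is not detail that an article may leave to a fuller document. The paragraph presents a finished calculation, and that calculation is for a secondary outcome. A non-significant responder result would be read as coming from a trial with 80% power, which these inputs do not support for that outcome.

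**Working it through.** **Inputs.** From Sample size calculation: means -7.1 (three times a week), -2 (sham) and -0.8 (blank control, taken as the waiting-list arm); SD 14.2; two-sided alpha 0.05; power 80%; 88 per group, 110 after dropout. From Primary outcome: the cut-off, a change of -4 or lower.

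**Step 1: reproduce the 88.**
- The mean of the three means is -3.3. The deviations are -3.8, 1.3 and 2.5, with squares summing to 14.44 + 1.69 + 6.25 = 22.38.
- Cohen's f = sqrt(22.38/3)/14.2 = 0.192.
- A three-group one-way ANOVA at alpha 0.05 and 80% power needs 87.8, so 88 per group (power at 88: 80.1%). Then 88/0.8 = 110, and 5 × 110 = 550.
- The other bases tried do not give 88. Two-sided pairwise tests of means need 122 per group against sham and 80 against blank control (one-sided 96 and 63). A five-group ANOVA with all acupuncture arms at -7.1 needs 62.

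**Step 2: pairwise power on means.** Power = Φ(difference/(14.2·sqrt(2/n)) − 1.96).
- Against sham, n = 88: 5.1/2.141 = 2.382, and Φ(0.422) = 66%. At n = 110: Φ(0.704) = 76%.
- Against blank control: 84% at 88 and 91% at 110.

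**Step 3: implied responder rates.** This assumes normal change scores with SD 14.2 in each arm. P(response) = Φ((−4 − mean)/14.2).
- Three times a week: Φ(3.1/14.2) = 58.6%.
- Sham: Φ(−2/14.2) = 44.4%.
- Waiting list: Φ(−3.2/14.2) = 41.1%.

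**Step 4: power on responders.** Two-proportion test, two-sided 0.05, unadjusted: power = Φ((sqrt(n)·d − 1.96·sqrt(2·p̄(1−p̄)))/sqrt(p1(1−p1) + p2(1−p2))).
- Against sham, n = 88: d = 0.1424 and p̄ = 0.515, so (1.336 − 1.385)/0.700 = −0.071, and Φ = 47%.
- The three-group chi-square has noncentrality n × 0.0174/0.2496, that is 6.13 at 88 and 7.67 at 110, on 2 degrees of freedom.

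| Comparison | Means, n = 88 | Responders, n = 88 | Responders, n = 110 |
|---|---|---|---|
| Three-group test | 80% | 59% | 70% |
| Against sham | 66% | 47% | 56% |
| Against waiting list | 84% | 65% | 74% |

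Simulation of 40,000 trials against sham gave 49% at 88 and 57% at 110, in line with the formula.

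**Step 5: what the planned size can detect.** With 44.4% responders on sham and 88 evaluable per arm, 80% power needs about 65% on acupuncture: (9.381 × 0.209 − 1.379)/0.688 = 0.84, and Φ(0.84) = 80%. That is a difference of about 21 percentage points. For scale only, 80% power for the implied 14-point difference would take about 193 evaluable per arm.

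**Step 6: other distribution shapes.** Keeping the same means and SD, power against sham at 88 and 110 per arm is:
- t with 5 degrees of freedom: 64% and 74%.
- Skewness +1: 45% and 54%.
- Skewness −1: 48% and 57%.

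**The case against.** A reader might infer that using a binary outcome takes 80% power down to 47%. The documents do not support that. The plan never says that the 80% is for acupuncture against sham, and 88 reproduces as a three-group test. Of the 33 points between 80% and 47%, about 14 (80% to 66%) arise because the calculation was not made for the sham comparison. The other 19 (66% to 47%) come from the change of outcome. This objection stands, and the like-for-like figures are the ones to quote.

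A reader might also infer that, on the plan's own assumptions, the primary result is close to a coin toss. That goes too far. The plan states means and one SD but not normality, and other shapes shift the figures. The description would also fit the sham comparison only. The plan singles out no decisive comparison, and its Discussion gives the waiting-list arm a purpose of its own.

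The 88 is moreover the number left after the maximum permitted dropout, while the analysis is by intention to treat with multiple imputation. The figure for 110, which assumes no information is lost, is the upper end of the range, and both ends should be given. Covariate adjustment and repeated visits in the mixed model may also shift power, but the documents give no inputs to quantify this.

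None of this supplies a responder rate or attaches the 80% to the primary outcome. Every shape tried stays below 80% against sham, even at 110 per arm.

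**Conclusion.** The concern holds as a mismatch of endpoint; the plan's arithmetic itself reproduces. The stated 80% fits a three-group comparison of mean SGRQ change. It is not the power for the responder outcome, nor for the sham comparison on either scale.

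Under normal change scores, SD 14.2 in each arm and unadjusted tests, responder power at 88 to 110 per arm is about 47% to 56% against sham, 65% to 74% against waiting list and 59% to 70% for the three-group test. At 88 per arm, the change of outcome accounts for a fall from 80% to 59% (three-group) or from 66% to 47% (against sham). The ANOVA basis is inferred from the reproduction, since the article does not name the test.

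**What to change.** Restate the sample-size paragraph; no extra patients and no change to the outcomes are needed. It should:

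- say that the 80% is reproduced by a three-group comparison of mean SGRQ change, and that it is not the power for responders or for the sham comparison. Saying only that it refers to mean SGRQ change would invite the reading that mean change has 80% power against sham, where it has 66% at 88 and 76% at 110;
- give the responder power from the table for 88 and 110 per arm, with the assumptions of normality, common SD and unadjusted tests;
- state that 88 evaluable per arm detects about a 21-percentage-point difference against sham (44% against 65%) with 80% power.

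Change in SGRQ is already a secondary outcome; moving it up the order would be a preference and would add no power for responders. The cost is rewording, and a stated power that looks less favourable.

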**Methods/design:**

This is a multicenter, randomized, controlled trial that uses central randomization to randomly allocate 550 participants in a 1:1:1:1:1 ratio to once a week acupuncture group, twice a week acupuncture group, three times a week acupuncture group, sham acupuncture group and waiting-list control group. The sham acupuncture group will receive placebo acupuncture treatments three times per week, and the waiting-list control group will not receive any form of acupuncture intervention. The study consists of a 2-week baseline, 12-week of treatment, and 52-week of follow-up. Patients with COPD between 40 to 80 years old who have received stable Western medication within the previous 3 months and have had at least 1 moderate or severe acute exacerbation within the past 1 year will be included in the study. Basic treatment will remain the same for all participants. The primary outcome is the proportion of responders at week 12. Secondary outcomes include the proportion of responders at week 64, change in the St. George's Respiratory Questionnaire (SGRQ) Scale, change in the Modified-Medical Research Council (mMRC) Scale, change in the COPD Assessment Test (CAT) Scale, change in the Lung Function Screening Indicators (LFSI), change in the 6-min walk distance (6-MWD), change in Short-Form 36 Health Survey (SF-36) Scale, the number of moderate and severe acute exacerbations and adverse event rate during the follow-up period.

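### The stated 80% power at 88 per group fits a three-group F test of mean SGRQ change; three-times-weekly versus sham has 66% power at that size

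*Protocol article*

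**What the plan says.** The section Sample size calculation (protocol article) assumes a mean SGRQ change of -7.1 with three-times-weekly acupuncture and of -0.8 in the blank control. For sham it has: "the mean change in SGRQ was -2 for patients in the SA group". One spread is used throughout, "with a standard deviation of 14.2". The error rate and sidedness are given as "Using a two-tailed test with a category 1 error of 0.05", and the result as "statistical efficacy of 80%, a sample size of 88 cases per group was calculated". Allowance for loss follows, "with a maximum of 20% of subjects allowed to drop out or disengage for a required sample size of 110 cases per group". The once- and twice-weekly groups take the same size without a calculation of their own, and the abstract gives the total, "randomly allocate 550 participants in a 1:1:1:1:1 ratio".

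The section does not say which statistical test produced 88, or which comparison has 80% power. Elsewhere in the article:

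- The first aim (Introduction) is to evaluate the efficacy and safety of acupuncture.
- The sham group has the same acupoints as the acupuncture groups, and the same three sessions a week and 36 sessions in total as the three-times-weekly group.
- The waiting-list group receives no needling.
- The primary outcome is the proportion of patients whose SGRQ total falls by at least 4 units at week 12.

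**The concern.** A two-tailed test at 0.05 with 80% power reads naturally as a comparison of two groups. In a trial with a frequency-matched sham arm and an efficacy aim, many readers will take it as acupuncture against sham. The assumed means do not support that reading, because the difference from sham is smaller than the difference from waiting list and needs many more patients than 88.

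Two things are at stake. First, a non-significant result against sham could be reported as the outcome of an adequately powered comparison when it was not one. Second, a significant three-group F test says only that the three means are not all equal. By itself it does not show that acupuncture is better than sham.

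**Working it through.** **Inputs**, all from Sample size calculation: means -7.1 (three times a week), -2 (sham), -0.8 (blank, i.e. waiting-list, control); SD 14.2, so variance 201.64; two-sided alpha 0.05; power 80%.

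**1. The plan's own figure.** One-way ANOVA with three equal groups of n:

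- Overall mean: (-7.1 - 2 - 0.8)/3 = -3.3.
- Squared deviations: 14.44 + 1.69 + 6.25 = 22.38.
- Non-centrality: n × 22.38/201.64. At n = 88 this is 9.77, with 2 and 261 degrees of freedom and critical F 3.03.
- Power: 0.796 at n = 87 and 0.801 at n = 88. The smallest n reaching 80% is **88**.
- Loss: 88/(1 - 0.20) = 110 per group, and 5 × 110 = 550.

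The chain 88, 110, 550 therefore reproduces in full.

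**2. Pairwise comparisons.** Normal approximation: n = 2 × (1.960 + 0.842)² × 201.64/d² = 3165/d². The t-test figure is the smallest n with at least 80% power from the non-central t.

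| Contrast with three times a week | d | n, normal | n, t test |
|---|---|---|---|
| Sham | 5.1 | 3165/26.01 → 122 | 123 |
| Waiting list | 6.3 | 3165/39.69 → 80 | 81 |
| One group at the average of the two controls | 5.7 | 3165/32.49 → 98 | 99 |

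None gives 88. Pooling both control arms (1:2) does not either: 1.5 × 7.849 × 201.64/32.49 = 73.1, so 74 in the acupuncture arm.

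**3. Power at the planned size.** Non-central t with non-centrality d/(14.2 × √(2/n)). At n = 88 this is 2.38 against sham and 2.94 against waiting list.

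| Setting | vs sham | vs waiting list |
|---|---|---|
| 88 per group, alpha 0.05 | 66% (0.659) | 83% (0.833) |
| 88 per group, alpha 0.025 each | 55% (0.549) | 75% (0.752) |
| All 110 observed, alpha 0.05 | about 76% | 91% |

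**4. F test against sham test.** I simulated 400,000 trials under the protocol's assumptions (normal data, 88 per group). The F test was significant in 80% and the sham t test in 66%. Both were significant in about 63%. In about 17% the F test was significant and the sham comparison was not.

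**5. The primary outcome's scale.** The protocol gives no responder rates, so this step assumes normally distributed changes with the stated means and SD. The responder rate is Φ((-4 - mean)/14.2):

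- Three times a week: Φ(3.1/14.2) = Φ(0.218) = 0.586.
- Sham: Φ(-2/14.2) = Φ(-0.141) = 0.444.

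At 88 per group a two-sided 0.05 comparison of 59% with 44% has 47% power with pooled variance under the null and 48% with unpooled variance.

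**The case against.** The strongest reply is that nothing in the section is miscalculated. Three means, one SD, 0.05 and 80% give 88 exactly, and listing the three means together suits a three-group calculation. The section never promises 80% power against sham. This stands. A reader might infer that 88 was meant to power the sham comparison, or that 88 is an arithmetic slip, and the document supports neither. What remains is that the test and contrast are unnamed, the description suggests a pairwise test, and the 80% does not carry over to the sham comparison.

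A reader might also infer that the F test is driven mainly by the waiting-list arm. It is not. Acupuncture against the average of the two controls accounts for 5.7² × 2/3 = 21.66 of the 22.38 (97%), and sham against waiting list for 1.2²/2 = 0.72 (3%). The assumed signal is acupuncture differing from both controls.

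The 17% in step 4 is a minority outcome, and nothing in Statistical analysis says that efficacy over sham will be concluded from an omnibus test. An analysis plan, not shown, may settle how contrasts are read. That limits the second consequence. It does not correct the power statement, which is made in this document.

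The two-tailed wording could simply be loose, since Statistical analysis applies two-sided testing to everything. That is fair, but it leaves the reader no better able to tell what has 80% power.

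Finally, the pairwise figures concern mean SGRQ change, which is a secondary outcome. That is correct, and the restated text must say so.

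**Conclusion.** The point holds as a misleading power statement and not as a calculation error. On the protocol's own assumptions, 88 per group gives 80% power for a three-group F test of mean SGRQ change. For three-times-weekly acupuncture against its frequency-matched sham, power is 66% with 88 evaluable. Intention-to-treat analysis with multiple imputation would put it between that and about 76%, the ceiling with all 110 observed. Either way it is below 80%, before any allowance for multiple contrasts.

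The pairwise and F-test figures rest on a common SD of 14.2, approximately normal changes, equal groups and unadjusted comparisons; they ignore any gain from covariates or repeated measurements. The responder figure of about 48% rests further on deriving responder rates from normal changes.

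**What to change.** Amend Sample size calculation as follows:

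1. State that 88 evaluable per group gives 80% power for a one-way F test of mean SGRQ change across three-times-weekly, sham and waiting-list groups, in place of the two-tailed description.
2. Report the pairwise power beside it: 66% against sham and 83% against waiting list at 88 per group, unadjusted, and 55% and 75% if each is tested at 0.025.
3. Name the contrast on which the efficacy conclusion will rest.
4. State that these figures are for mean change and not for the primary responder proportion, and give the responder-scale power with its assumption (about 59% versus 44%, roughly 48% power against sham at 88).

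This is a change of text only. It adds no patients and leaves design and analysis as they are. Its cost is that a less favourable power figure is on record, so that a non-significant result against sham can be read for what it is.
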